#### Regimen

Each patient will receive successively in random order each of the three products with a period of washout between every administration. The duration of the washout will be 5 weeks (35 days). The duration of each infusion is 2½ h per patient as follows:
*Ketamine-placebo group:* Ketamine will be administered for 2 h and placebo for 30 minutes.
*Ketamine-magnesium sulfate group:* Ketamine will be administered for 2 h and magnesium sulfate for 30 minutes.
*Placebo-placebo group:* Placebo will be administered for 2 h and placebo for 30 minutes.

The drugs used in the study (ketamine, ketamine-magnesium, and placebo) are prepared, conditioned, and released in the hospital pharmacy by one qualified person according to good manufacturing principles. Once the treatment is completed, the empty infusion bags are then returned to the packaging box, and the number of infusion bags in each dispensed container is verified and recounted at the end of the treatment by two persons totally independent of the protocol.

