### Objective

The primary objective of this study is to compare, using a crossover design, the analgesic efficacy of intravenous ketamine with that of placebo in patients with intractable NP. Secondary objectives are as follows:To compare the additive analgesic efficacy of magnesium and ketamineTo study the time course of pain and analgesia after intravenous administration of ketamine, ketamine-magnesium, and placebo

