### Sample size calculation

To highlight the analgesic efficacy of intravenous ketamine in patients with intractable NP, sample size estimation was based on a pilot study done at the pain clinic of the University Hospital of Clermont-Ferrand (administration of intravenous ketamine in a similar open-label population), showing an AUC (28 days) of the intensity of pain of 164 ± 38 (unpublished data). Furthermore, in a study comparing similar treatments (ketamine and placebo) in a different chronic pain setting (CRPS), the AUC graph estimate suggested a 35% reduction in AUC (at 28 days), that 18 patients are needed to detect a minimum difference of 57 in the primary outcome, with a two-sided type I error of 1.67% (to take account of multiple comparisons), statistical power of 90%, and an intraindividual correlation coefficient of 0.5 (owing to the crossover design and no carryover effect assumed) [46]. Considering data from our center, a recent study [46] (NCT01602185) currently submitted to a peer-reviewed journal but not yet published clearly shows that pain evaluation remains the same from 28 days to 60 days. Ultimately, allowing for patient dropout for adverse events or premature withdrawal, we plan to recruit 22 subjects.

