### Statistical analysis

Statistical analysis will be performed on an intention-to-treat basis using Stata software (version 13; StataCorp, College Station, TX, USA) for a two-sided type I error at α = 5%. Continuous data will be described as mean ± SD or median (IQR) according to the statistical distribution (assumption of normality studied by Shapiro-Wilk test). Categorical parameters will be described as number and percent. The primary endpoint (AUC of pain intensity based on NPRS) will be compared between groups by repeated measures analysis of variance (ANOVA) for crossover designs, taking account of the following effects: treatment group (ketamine versus placebo), sequence, subject (as random effect), and carryover. Then, the “sequence × treatment” interaction will be tested; if it is significant, statistical analysis will cover only the first period of the crossover study. The normality of residuals will be studied. When quantitative endpoints do not meet the normality assumption, a nonparametric paired Wilcoxon test will be used. Sensitivity analysis will determine the statistical nature of missing data to apply the most appropriate imputation approach.

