Statistical analyses of secondary outcomes (NPSI, BPI, HAD, SF-36, PSQI and McGill Pain Questionnaire scores) will be performed similarly to those for the primary endpoint. For categorical parameters (PGIC, analgesic response), the Stuart-Maxwell test for proportion paired data or a generalized linear mixed model will be used, taking the above effects into account. Random-effects models, useful to model between- and within-subject variability, will be performed for the effects described for the crossover ANOVA, to compare the additive analgesic efficacy of associating magnesium sulfate versus placebo to ketamine, and to study the evolution of pain and analgesia with the waning of the intravenous administration. In case of omnibus *p* value < 0.05, a post hoc analysis for multiple comparisons (inflation of type I error) will be applied using the Tukey-Kramer test. For non-crossover comparisons, the usual statistical tests will be performed: (1) for quantitative parameters, ANOVA or Kruskal-Wallis test if the conditions for parametric tests are not met (normality and homoscedasticity on Fisher-Snedecor test); and (2) for categorical variables, the chi-square test or Fisher’s exact test. When appropriate (*p* < 0.05), an appropriate post hoc test will be applied: Tukey-Kramer post hoc ANOVA or Dunn post hoc Kruskal-Wallis. As discussed by Feise [47], type I error (α) will not be adjusted systematically, but rather on a case-by-case basis, in the light of clinical rather than exclusively statistical considerations.

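### The planned ketamine-magnesium v ketamine contrast falls under an omnibus gate plus Tukey-Kramer: valid, but with three treatments stricter than 5% family-wise control requires

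*Protocol article*

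**What the plan says.** All references are to the protocol article.

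- **Design (Regimen).** There are three treatments, all within patient: "Each patient will receive successively in random order each of the three products".
- **Objectives (Objective).** "The primary objective of this study is to compare, using a crossover design, the analgesic efficacy of intravenous ketamine with that of placebo". The added effect of magnesium is listed as a secondary objective.
- **Model for the magnesium question (Statistical analysis).** Random-effects models are to be used "to compare the additive analgesic efficacy of associating magnesium sulfate versus placebo to ketamine", among other purposes.
- **Pairwise rule (same section, next sentence), which names Tukey-Kramer as the method.** "In case of omnibus *p* value < 0.05, a post hoc analysis for multiple comparisons (inflation of type I error) will be applied using the" …
- **Alpha.** Three statements bear on it. The Statistical analysis section opens with analysis "for a two-sided type I error at α = 5"%. The Sample size calculation works "with a two-sided type I error of 1.67% (to take account of multiple comparisons"). The Statistical analysis section closes by saying that "type I error (α) will not be adjusted systematically, but rather on a case-by-case basis". The abstract adds that every test other than the primary analysis is at 5%.
- **Power.** The Sample size calculation assumes "statistical power of 90%, and an intraindividual correlation coefficient of 0.5" for a difference of 57 AUC units, derived from a ketamine v placebo setting. It gives no effect size or power for the magnesium contrast.

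**The concern.** The magnesium question is a single contrast fixed in advance, but the pairwise rule treats it as exploratory. It must pass a three-treatment omnibus test and then a Tukey-Kramer threshold. Each device is a recognised way to limit false positives across three pairs. Tukey-Kramer does so without a gate, and with three treatments the gate does so without Tukey-Kramer.

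What is at stake is power on a stated objective. The effect of adding magnesium to an active drug may well be smaller than the 57 units used for sizing. Small to moderate effects are where a stricter threshold costs most, so the plan raises the chance of missing a real magnesium effect without needing to.

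**Working it through.** **The plan's own figure.** The only sample size or power figure is 18 patients for a difference of 57. The paired formula on the stated inputs gives n = [38 × (2.393 + 1.282) / 57]² = 6.0, so 7 patients (10 with the t distribution). The stated 18 is therefore not reproduced. That is a separate matter; here 18 and 22 serve only as the numbers of patients analysed.

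**Inputs.** From the Sample size calculation: SD 38, correlation 0.5, ketamine effect 57, n = 18 (22 recruited). Assumed: true ketamine-magnesium v ketamine differences of 20 to 57 AUC units, normal errors, no carryover term, and residual df = 3n − n − 2 − 2 = 2n − 4 (patients, periods, treatments), which is 32 at n = 18 and 40 at n = 22. The SD is for a 28-day AUC.

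**Step 1: why the gate is enough with three treatments.** There are three pairwise null hypotheses. If any two are true, all three treatments are equal, so every intersection is the global null. The closed family is the global null plus the three single pairs. Rejecting a pair when both the omnibus test and that pair's own test are significant at 5% therefore keeps the family-wise error at 5% or less.

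**Step 2: thresholds.** SD of a within-patient difference = 38 × √(2 × (1 − 0.5)) = 38. SE at n = 18 is 38/√18 = 8.96.

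- Unadjusted 5%: critical value 2.04, so an observed difference of about 18.2 units is significant (2.037 × 8.96).
- Tukey-Kramer: critical value 2.46, so about 22.0 units (2.457 × 8.96). This is a per-comparison level of 1.96%.

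At n = 22 the critical values are 2.02 and 2.43.

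**Step 3: family-wise error** (200,000 simulated trials per scenario, n = 18 and 22).

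| Truth | Gate + 5% tests | Gate + Tukey-Kramer |
|---|---|---|
| All three equal | 5.0% | 4.5% |
| Ketamine = ketamine-magnesium, both 57 from placebo | 5.0% | 1.9–2.0% |

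**Step 4: power for ketamine-magnesium v ketamine**, with ketamine 57 units from placebo.

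| n | Assumed effect | Gate + 5% | Gate + Tukey-Kramer | Loss (points) |
|---|---|---|---|---|
| 18 | 20 | 58% | 42% | 16 |
| 18 | 25 | 77% | 63% | 14 |
| 18 | 28 | 86% | 75% | 11 |
| 18 | 35 | 97% | 92% | 5 |
| 18 | 57 | 100% | 100% | 0 |
| 22 | 20 | 67% | 52% | 15 |
| 22 | 25 | 85% | 74% | 11 |
| 22 | 28 | 92% | 84% | 8 |
| 22 | 57 | 100% | 100% | 0 |

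If ketamine equals placebo, the gate limits both procedures and the loss is at most about 9 points (at n = 22 and 20 units, 60% v 51%).

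**Step 5: source of the loss.** Tukey-Kramer without the gate has almost the same power as with it; the gate costs it under 1 point in these scenarios. The loss is due to the Tukey threshold.

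**The case against.** - **The stated procedure is valid.** An omnibus test followed by Tukey-Kramer is conventional, controls the family-wise error and permits simultaneous intervals. This stands: the point concerns efficiency, not error control. The protocol does not, however, say that it wants simultaneous intervals.
- **The sizing alpha is already stricter.** At 1.67% and df 32 the critical value is 2.53, above Tukey's 2.46. An effect with 90% power at 1.67% has 91% with Tukey-Kramer and 96% with 5% tests. Against the sizing level, then, Tukey-Kramer loses nothing. But 1.67% is an allowance made when sizing the trial, whereas the analysis section sets 5%. It does not make a second correction necessary.
- **The text may leave a way out.** The magnesium model and the Tukey-Kramer rule stand in consecutive sentences, and nothing says that the contrast is tested only by that route. The case-by-case sentence could be read as allowing an unadjusted planned test. This is fair, and it is a reason to fix one rule now: as written, the choice could be made after the data are seen.
- **The contrast is secondary.** A reader might infer from the title that magnesium is the trial's main question. The Objective section does not support that, and the lack of a separate power statement for a secondary contrast is not in itself a fault.
- **An interval reported after a failed gate could conflict with the test.** This stands, so such an interval should be labelled descriptive.

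**Conclusion.** The point holds as a cheap improvement. For the three-treatment comparisons, the Tukey-Kramer step is not needed for 5% family-wise control. When ketamine works, it moves the magnesium test from 5% to about 2%. Because 2.04 is below 2.46, the gate with 5% tests is never less powerful than the stated rule.

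The size of the loss is conditional. It runs from 0 to about 16 points, and the magnesium effects behind it are assumptions. A reader might take 11 to 16 points as a general figure. It applies only to true differences of about 13 to 28 units at n = 18 (11 to 25 at n = 22), and only if ketamine clearly differs from placebo. Fitting the carryover term that the protocol names would lower power under both rules.

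Two further inferences are not supported. The plan does not inflate type I error here. Nor is Tukey-Kramer worthless, since it permits simultaneous intervals. The closed-testing argument covers three treatments on one endpoint under the ANOVA assumptions; it gives no protection across the many secondary endpoints.

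**What to change.** For the three-treatment crossover comparisons, replace the Tukey-Kramer sentence with wording such as:

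> If the three-treatment omnibus test has p < 0.05, each pairwise contrast is tested from the same mixed model at two-sided 5%; with three treatments this closed procedure controls the family-wise error at 5%.

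Then:

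1. Name ketamine-magnesium v ketamine as a planned secondary contrast, not a post hoc one.
2. Report its estimate with a 95% CI whatever the omnibus result, labelled descriptive if the gate fails.
3. Reconcile this rule with the 1.67% in the Sample size calculation, the 5% in the Statistical analysis section and abstract, and the case-by-case sentence. State which level applies to the primary ketamine v placebo test and whether that test belongs to the three-pair family.

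The cost is a sentence or two in the protocol and in any SAP, with no extra patients or data. The one statistical downside is that the pairwise intervals are no longer simultaneous. If the sponsor wants simultaneous intervals and keeps Tukey-Kramer, it should say so; items 1 and 3 still apply.

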**Methods/design:**

A randomized, double-blind, crossover, placebo-controlled study will be performed in Clermont-Ferrand University Hospital, Clermont-Ferrand, France. The aim is to evaluate the effect of ketamine with or without magnesium in 22 patients with neuropathic pain. Intravenous ketamine/placebo, ketamine/magnesium sulfate, or placebo/placebo will be administered consecutively to each patient, in random order, once at 5-week intervals. The primary endpoint is the AUC of pain intensity assessed on a 0–10 Numeric Pain Rating Scale for a 5-week period. Data analysis will be performed on an intention-to-treat basis, and all statistical tests (except primary analysis) will be performed with an α risk of 5% (two-sided).

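### The primary test has no single stated significance level: the sizing and abstract point to 1.67%, but the analysis section says 5% without exception

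*Protocol article*

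**What the plan says.** Four places in the protocol article bear on the significance level of the primary test.

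- **Sample size calculation.** Eighteen patients are required to detect a difference of 57 in the primary AUC "with a two-sided type I error of 1.67% (to take account of multiple comparisons"), with 90% power.
- **Abstract, Methods/design.** It states that "all statistical tests (except primary analysis) will be performed with an α risk of 5% (two-sided"). The primary analysis is thus exempted from 5%, but no figure is given for it.
- **Statistical analysis, first paragraph.** Analyses are planned "for a two-sided type I error at α = 5"%. The primary model follows in the same paragraph, with effects for "treatment group (ketamine versus placebo), sequence, subject (as random effect), and carryover". No exception is made for it.
- **Statistical analysis, second paragraph.** It opens: "Statistical analyses of secondary outcomes (NPSI, BPI, HAD, SF-36, PSQI and McGill Pain Questionnaire scores) will be performed similarly" to the primary endpoint. It goes on to the magnesium comparison and the time course, and adds: "In case of omnibus *p* value < 0.05, a post hoc analysis for multiple comparisons (inflation of type I error) will be applied", using Tukey-Kramer. It ends by saying that "type I error (α) will not be adjusted systematically, but rather on a case-by-case basis", on clinical rather than purely statistical grounds. That last sentence names no endpoint or comparison.

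The Objective section makes one contrast primary: "the analgesic efficacy of intravenous ketamine with that of placebo in patients with intractable NP". The added effect of magnesium is a secondary objective.

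**The concern.** The section that governs the analysis gives a different level from the one on which the trial was sized. The level decides whether the trial is positive, so this is a conflict between stated rules and not a detail left for later. The last sentence of the section makes it worse: because its scope is open, it could be cited in support of either level once the p-value is known.

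The stake is the primary conclusion of a 22-patient single-centre trial that is meant to inform practice recommendations. If the result falls between the two levels, the document supports both a positive and a negative reading.

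**Working it through.** **1. Origin of 1.67%.** 0.05 / 3 = 0.0167. This is a Bonferroni split over three comparisons, which fits the three pairwise contrasts among three treatments. The document does not list the three.

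**2. The plan's own figure.** Inputs from Sample size calculation: SD 38, correlation 0.5, difference 57, power 90%, two-sided alpha 1.67%.

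- SD of the within-patient difference = 38 × √(2 × (1 − 0.5)) = 38.
- n = ((z for alpha/2 + z for power) × SD of difference / difference)².
- At 1.67%: ((2.39 + 1.28) × 38/57)² = 6.0, or 10 with the exact noncentral t.
- At 5%: ((1.96 + 1.28) × 38/57)² = 4.7, or 7 with the exact noncentral t.

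The stated 18 is not reproduced at either level. That is a separate matter and does not decide this point, but it limits what can be said about power in step 5.

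**3. The statements side by side, for ketamine versus placebo on the primary AUC.**

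| Place | Level for the primary test | p between 0.0167 and 0.05 |
|---|---|---|
| Sample size calculation | 1.67% | negative |
| Abstract | not 5%; no figure given | negative, if read with the sample size section |
| Statistical analysis, first paragraph | 5%, no exception | positive |
| Statistical analysis, second paragraph (last sentence) | scope not stated | undetermined |

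**4. Size of the conflict.** For the single named primary contrast, the false-positive risk is the level itself: 5% or 1.67%, and 5 / 1.67 = 3.0.

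**5. Cost in power of holding 1.67% (paired t, 18 patients, difference 57).**

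| SD of difference | Basis | Power at 1.67% | Power at 5% |
|---|---|---|---|
| 38 | the stated SD and correlation | 99.97% | above 99.99% |
| about 60 | value at which 18 patients give the stated 90% | 90% | 97% |

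The two rows cannot both be right, because the stated inputs do not give the stated power. The cost is therefore between almost nothing and about 7 percentage points.

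**6. Family-wise error if all three pairwise contrasts on the primary AUC were tested.** Simulated under the global null:

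- Each at 5% with no adjustment: 12.2%.
- Each at 1.67%: 4.4%.
- Tukey-Kramer (18 patients, three treatments): 5.0%, or 4.5% when it follows a significant omnibus test.

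With 34 degrees of freedom Tukey-Kramer corresponds to a per-pair level of about 1.96%, close to 1.67% but not equal to it.

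**The case against.** **The intended level can be inferred.** The abstract removes the primary analysis from 5%, and the sample size section supplies the only other figure. The two agree on 1.67%, so the defect may be no more than a missing exception in the analysis section. This stands as the best reading of intent. It does not remove the conflict, because it asks the reader to overrule the section that contains the primary model.

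**A reader might infer three definite rules for the primary test: 1.67%, 5% and case by case.** The document does not support that. The case-by-case sentence closes a paragraph that opens with secondary outcomes and deals with post hoc tests. It is a loose end that needs a scope, not an established rule for the primary contrast.

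**A reader might infer a family-wise error of 12%.** That needs three primary contrasts tested at 5% each without adjustment. The Objective section and the primary model name only one contrast. If the second paragraph were applied to all three, it would bring Tukey-Kramer with it, which holds the error at about 5%. Only the case-by-case sentence overriding Tukey-Kramer would give 12%, and that is a worst-case reading.

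**A single primary contrast at 5% would be a valid design.** True. The problem is not that 5% is wrong in itself, but that the document commits to two levels.

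**This is a condensed article, and an analysis plan may settle the level.** It may. But the article states two incompatible levels; it does not merely leave one out. So it needs correcting in either case.

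**Conclusion.** The point holds as an inconsistency in the stated level for the primary test. The sample size section and the abstract point to 1.67%; the analysis section says 5% without exception and is followed by an unscoped statement on adjustment. The consequence is that p-values between 0.0167 and 0.05 for ketamine versus placebo have no determined meaning, with a false-positive risk of 5% against 1.67%.

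This rests on ketamine versus placebo being the only primary contrast, as the Objective section says, and on the article being read as it stands, without the full protocol or analysis plan.

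It would also go too far to say that the stricter level is free. The 99.97% power comes from inputs that do not reproduce the plan's own 90% at 18 patients, so a loss of up to about 7 percentage points relative to testing at 5% has to be allowed for.

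**What to change.** In the first paragraph of Statistical analysis:

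- State that ketamine versus placebo on the primary AUC is tested two-sided at 1.67%, the level used for sizing, and reported with a 98.33% confidence interval (100 − 1.67).
- Name the comparisons that the 1.67% is meant to cover, since the Objective section names one primary contrast and the division by three implies three.
- Limit the 5% level to all other tests, as the abstract already does.

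In the second paragraph, say expressly that the omnibus/Tukey-Kramer rule and the case-by-case sentence apply only to analyses other than this primary contrast. Tukey-Kramer need not be replaced for those analyses; that would be a matter of preference.

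The change is wording only and needs no new patients or data. The article reports recruitment as ongoing, so the change should be made and dated before the data are unblinded. Its price is the stricter threshold, with power of about 90% instead of about 97% if the plan's stated power is right.

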## Discussion

Persistent pain is difficult to treat, and a range of evidence indicates that NMDARs play an important role in sensitization, windup, and neuroplastic changes in the central nervous system [48]. Ketamine may reduce NP symptoms via its antagonistic action on NMDARs [49–51]. Magnesium, a physiological blocker of the NMDAR calcium channels, has also been shown to be effective in the treatment of NP, such as postherpetic neuralgia, CRPS, and phantom limb pain [51–53]. Researchers in two studies examined the effect of these antagonists, and the results were contradictory. Felsby et al. [49] reported that ketamine was more effective than magnesium in the treatment of chronic NP, whereas Kim et al. [51] did not find a significant difference between the two. This discrepancy may have been due to a difference in magnesium dose and administration time. Ketamine and magnesium were given separately but never in combination, and the major limitation of these clinical studies is that they had no placebo group. The objective of the present study is to compare three different forms of injection (ketamine alone, ketamine-magnesium, and placebo) to optimize analgesia in patients with severe NP. Although ketamine, associated with magnesium sulfate or not, is often administered for NP, physicians have no reliable guidelines for prescribing it.

Furthermore, it is also widely reported that NP is known to impact quality of life with psychological discomfort, anxiety, and/or depression [54]. Recently, an open-label study showed that oral administration of ketamine improved both depression and anxiety symptoms [55]; a single injection was sufficient to reduce refractory depressive symptoms after 2 h and for 1 week [56]. The present clinical trial will also evaluate the efficacy of the three injections on the emotional component of pain and on the comorbidities associated with chronic pain.

The benefit expected for participating patients lies in better follow-up of pain and quality of life, with no additional risk. This double-blind randomized controlled clinical trial will provide objective data on the efficacy of ketamine in the treatment of NP and comorbidities associated with chronic pain, such as anxiety and depression. It will enrich good practice recommendations for ketamine, an anesthetic that is often used off-label for NP.

